## STUDY SUMMARY

### Phase 2 Study of Tenofovir Disoproxil Fumarate (TDF) for Prevention of HIV

#### Study 9780

|                            |                                                                                                                                                                                                                                                                                                                            |
|----------------------------|----------------------------------------------------------------------------------------------------------------------------------------------------------------------------------------------------------------------------------------------------------------------------------------------------------------------------|
| Design:             | Phase 2, multi-center, fully-masked, randomized, parallel, placebo-controlled effectiveness and extended safety study to assess the role of TDF as prophylaxis to prevent HIV acquisition                                                                                                                                  |
| Population:         | 1,200 HIV antibody negative participants:
600 participants will use TDF daily
600 participants will use placebo daily                                                                                                                                                                                                |
| Study Duration:     | 6 months screening, 6 months recruitment, 12 months of product use for each participant, 20 months in the field, including screening and close-down                                                                                                                                                                        |
| Primary Objectives: | Determine the effectiveness and safety of daily use of 300 mg TDF for HIV prevention                                                                                                                                                                                                                                       |
| Primary Endpoints:  | 
Incidence of HIV-1 and HIV-2 infection as determined by detection of HIV antibodies from oral mucosal transudate (OMT) specimens and confirmation by ELISA.
 
Incidence of liver and kidney events as determined by AST and ALT for hepatic function, and serum creatinine and phosphorus for kidney function.
 |
| Study Sites:        | Douala, Cameroon
Ibadan, Nigeria
Tema, Ghana                                                                                                                                                                                                                                                                         |

## LIST OF ABBREVIATIONS AND ACRONYMS

|                 |                                                                  |
|-----------------|------------------------------------------------------------------|
| AE              | adverse event                                                    |
| AIDS            | acquired immunodeficiency syndrome                               |
| ALT (SGPT)      | alanine aminotransferase                                         |
| AST (SGOT)      | aspartate aminotransferase                                       |
| DCF             | data collection forms                                            |
| DMC             | Data Monitoring Committee                                        |
| eDCF            | electronic data collection form                                  |
| ELISA           | enzyme-linked immunosorbent assay                                |
| FDA             | (U.S.) Food and Drug Administration                              |
| g               | gram(s)                                                          |
| GCP             | Good Clinical Practice guidelines                                |
| HAART           | highly active antiretroviral therapy                             |
| HIV-1           | human immunodeficiency virus type 1                              |
| HIV-2           | human immunodeficiency virus type 2                              |
| ICH             | International Conference of Harmonisation                        |
| IRB             | Institutional Review Board                                       |
| ITT             | intent-to-treat                                                  |
| IU              | international units                                              |
| kg              | kilogram(s)                                                      |
| LLN             | lower limit of the normal range                                  |
| LLOQ            | lower limit of quantification                                    |
| mg              | milligram(s)                                                     |
| mL              | milliliter(s)                                                    |
| mm  | cubic millimeter(s)                                              |
| NNRTI           | non-nucleoside reverse transcriptase inhibitor                   |
| NRTI            | nucleoside reverse transcriptase inhibitor                       |
| NtRTI           | nucleotide reverse transcriptase inhibitor                       |
| OMT             | oral mucosal transudate                                          |
| PCR             | polymerase chain reaction                                        |
| PharmaLinkFHI   | a contract research organization responsible for data management |
| PrEP            | pre-exposure prophylaxis                                         |
| RT              | reverse transcriptase                                            |
| SAE             | serious adverse event                                            |
| TDF             | tenofovir disoproxil fumarate, GS-4331-05, PMPA prodrug          |
| µg              | microgram                                                        |
| ULOQ            | upper limit of quantification                                    |
| ULN             | upper limit of the normal range                                  |

# 1. INTRODUCTION

## 1.1 Background

The HIV epidemic is continuing to grow worldwide. An effective, easy to use method of prevention is urgently needed. Consistent and correct condom use is the only method currently recommended for prevention of sexually transmitted HIV. Vaginal microbicides are being developed in the hopes of offering women a method to protect themselves from infection when condom use is not possible. However, no vaginal microbicide candidate has shown effective protection from HIV in human trials.

TDF is an orally bioavailable prodrug of tenofovir, an acyclic nucleotide analog with activity in vitro against retroviruses, including HIV-1, HIV-2, and hepadnaviruses.

The non-clinical toxicology of TDF has been studied in mice, rats, rabbits, and dogs. The principal target organs of toxicity following oral administration of TDF were the gastrointestinal tract, kidney, and bone.

The safety profile of TDF is primarily derived from clinical studies. There has been no evidence of renal toxicity related to TDF. Laboratory evaluation of serum creatinine and phosphorus has not demonstrated a difference between TDF and placebo or other active controls.

Evidence suggests that oral, once-daily TDF 300 mg appears comparable to placebo for safety and has durable efficacy in HIV-1-infected patients with high levels of baseline resistance to nucleoside reverse transcriptase inhibitors. The FDA has approved 300 mg TDF per day as safe and effective for treatment for HIV infection. TDF has received marketing approval in the European Union. No marketing authorizations have been withdrawn or suspended, and no marketing authorizations have been denied. No clinical trials have been suspended, there have been no dosage modifications since approval, and no changes in target populations, labeling, or formulation changes for safety reasons since approval.

Furthermore, animal studies provide strong support for both the pre-exposure as well as post-exposure efficacy of TDF in preventing retroviral infections. These studies include challenge by both the intravenous and intravaginal modes of SIV infection as well as vertical transmission to neonate macaques.

Tenofovir was found to have potent activity in an acute challenge experiment of simian immunodeficiency virus (SIV) infection in monkeys, a model of needlestick injury. When treatment was started as late as 24 hours after intravenous SIV inoculation and continued for four weeks, tenofovir was found to completely protect the animals from SIV infection without signs of toxicity.

By intravaginal administration topically, tenofovir also was completely protective against vaginal transmission of SIV in another simian model. Such activity of an antiviral compound in

animal models is unprecedented and makes tenofovir a promising agent for both treatment and prevention of HIV infection.

The safety of TDF has been established with regard to its use in combination with other antiretrovirals for HIV-infected persons. However, the safety profile for healthy, uninfected persons or for uninfected persons with conditions such as malaria has not been established.

This Phase 2 study will evaluate the effectiveness of TDF 300 mg as an HIV prevention method when taken once a day. This Phase 2 study in three countries will provide extended safety data for high-risk populations in those countries. The daily tablet of TDF will allow disassociation of the preventive method from the type of coitus (wet vs. dry), number of coital acts, the timing of the coitus, the place of coitus, or other sexual activity such as anal or oral sex.

We will study the effectiveness and safety of TDF in a population of young women at high-risk for HIV infection.

## **1.2 Rational**

TDF has been selected for investigation as prophylaxis against HIV in high-risk young women because of its unique pharmacologic profile. In addition to the convenience of being a once daily single tablet, TDF's safety profile is comparable to placebo among HIV infected persons, it has striking anti-HIV potency, and it has low potential for selection of resistant viruses. TDF is cleared from the body by the kidneys and is not metabolized by the liver. Therefore, TDF has limited potential to have pharmacokinetic interactions with other hepatically metabolized drugs. Each of these properties is necessary given the realities of the intended target populations. Moreover, initial prevention studies in simian models have provided encouraging results. Finally, the drug's sponsor, Gilead Sciences, is supportive of investigating the potential use of TDF as a preventive, as well as therapeutic, agent and will provide TDF for the study. Gilead also is willing to make a good faith effort to make TDF available for public health use should it prove to be effective for HIV prevention.

Condoms and potential vaginal microbicides require consistent and correct use during every coital act. This is similar to the situation when barrier methods were the most common forms of nonpermanent contraception. However, when hormonal oral contraceptives were introduced and the preventive method became disassociated with coitus, contraception become easier, popular, and more effective at the individual and population level. If successful, this drug has the potential to do for HIV prevention what oral contraceptives did for pregnancy prevention.

## **2. STUDY OBJECTIVES**

### **2.1 Primary Objectives**

- To assess the effectiveness of TDF 300 mg use by young women at high risk for HIV in countries that will be suitable for the introduction of TDF as a preventive intervention
- To assess the extended safety of TDF 300 mg per day among women who are not HIV infected

Comparing the HIV incidence in the TDF group with that in the control group will assess effectiveness.

Comparing data on changes in kidney and liver function, as well as the frequency of adverse events in the TDF group with that in the control group will assess extended safety.

## **3. TRIAL DESIGN**

This Phase 2 clinical trial will be conducted in compliance with the protocol, FHI SOPs, Good Clinical Practices (ICH/GCP), and the applicable regulatory requirements of the FDA and the site countries.

### **3.1 Primary Endpoints**

The effectiveness endpoint is conversion for antibodies to HIV 1 or 2 as determined by an OMT test and confirmed by an ELISA from a finger prick specimen. Discordant results between the OMT and the ELISA will be tested with Western blot.

Laboratory safety endpoints will include serum creatinine and phosphorus for kidney function, and AST and ALT for hepatic function. Reported adverse events will also be used for clinical evaluation of safety.

### **3.2 Study Design**

This protocol describes a multi-center, randomized, fully-masked, parallel, placebo-controlled study of TDF for pre-exposure prophylaxis of HIV in high-risk women.

One thousand two hundred women from Douala, Cameroon, Ibadan, Nigeria and Tema, Ghana will be randomized 1:1 to once daily use of TDF 300 mg or placebo. Each country will contribute 400 participants to the study. Recruitment of participants will take about 6 months and each participant will be followed for 1 year.

HIV status will be monitored monthly. Participants will be monitored for safety using periodic physical examinations, serial laboratory tests, and adverse event queries.

In order to provide sufficient information for early safety monitoring, we will conduct laboratory tests for kidney and liver function at screening and then at months 1, 3, and then every 3 months thereafter or at their final visit if they withdraw early.

To minimize their risk of contracting HIV infection, women will be counseled monthly to use male condoms every time they have intercourse. Male latex condoms will be provided to participants. Participants converting for antibodies to HIV will be counseled and referred to medical services as appropriate for each country.

### **3.3 Measures to Minimize Bias**

#### ***3.3.1 Randomization***

The Randomization Manager who is not otherwise involved with the study will develop the allocation sequence using a computer random number generator and randomly varied permuted-blocks. Participants will be assigned their randomization number only after they have qualified for the study and signed the consent form. Randomization will be stratified by study site.

#### ***3.3.2 Allocation concealment***

Individual assignments will be concealed in sequentially numbered, sealed opaque envelopes. Trained staff will open the envelopes only after participants are properly consented and enrolled. The randomization envelopes will be maintained in a secure office. They will not be available to the study counselors until the immediate moment of randomization. Each randomization envelope will be used only once and maintained in the participant's study files.

#### ***3.3.3 Masking***

Placebo tablets to match the TDF tablets are available, and contain denatonium benzoate to provide a bitter taste to resemble the active tablets. The participants, field study staff, monitors, statisticians, and FHI staff actively involved in the trial will not know which participants are using TDF and which are using placebo.

#### ***3.3.4 Decoding procedure***

The FHI Randomization Manager will keep the randomization code. The Manager will provide the code to the FHI Study Clinician if needed to reveal the masking to the Investigator for emergencies. The Manager will provide the code to the DMC during meetings to review the interim data. The Manager will provide the code to the statisticians when they are prepared to unmask the code after completion of the final masked analysis of the data.

### **3.4 Study Product**

Tenofovir (PMPA), 9-[(R)-2-(phosphonomethoxy)propyl] adenine monohydrate) is an acyclic nucleotide analog with activity in vitro against retroviruses, including HIV-1 and HIV-2. Tenofovir is metabolized intracellularly to tenofovir diphosphate (PMPApp), which is a

competitive inhibitor of HIV-1 reverse transcriptase (RT) that terminates the growing DNA chain.

Due to the presence of a phosphonate group, tenofovir has limited oral bioavailability. Tenofovir disoproxil fumarate (tenofovir DF, (9-[(R)-2-[[bis[(isopropoxycarbonyl)oxy] methoxy]phosphinyl]methoxy] propyl] adenine fumarate)) is a prodrug of tenofovir. Tenofovir DF (TDF) is orally bioavailable in animals and humans and is rapidly converted to tenofovir following absorption.

Treatment-Related Adverse Events (Grades 1-4) Reported in >3% of VIREAD-Treated Patients in the Pooled 902 - 907 Studies (0-24 weeks)

|                            | VIREAD
300 mg | Placebo |
|----------------------------|------------------|---------|
| Number of patients treated | 443              | 210     |
| Nausea                     | 11%              | 10%     |
| Diarrhea                   | 9%               | 8%      |
| Asthenia                   | 8%               | 8%      |
| Headache                   | 6%               | 7%      |
| Vomiting                   | 5%               | 2%      |
| Flatulence                 | 4%               | 0%      |
| Abdominal Pain             | 3%               | 3%      |
| Anorexia                   | 3%               | 1%      |

Grade 3/4 Laboratory Abnormalities Reported in  $\geq 1\%$  of VIREAD-Treated Patients in the Pooled 902 - 907 Studies (0-24 weeks)

|                                                               | VIREAD
300 mg | Placebo  |
|---------------------------------------------------------------|------------------|----------|
| Number of patients treated                                    | 443              | 210      |
| Number of patients with Grade 3 or 4 laboratory abnormalities | 117 (26%)        | 78 (37%) |
| Laboratory abnormalities                                      |                  |          |
| Triglyceride (>750 mg/dl)                                     | 37 (8%)          | 28 (13%) |
| Creatine Kinase (>782 U/L)                                    | 53 (12%)         | 38 (18%) |
| Serum amylase (>175 U/L)                                      | 21 (5%)          | 14 (7%)  |
| AST
Male >180 U/l
Female >170 U/L                       | 16 (4%)          | 6 (3%)   |
| Urine glucose (3+ or 4+)                                      | 12 (3%)          | 6 (3%)   |
| ALT elevation
Male >215 U/L
Female >170 U/L             | 10 (2%)          | 4 (2%)   |
| Serum glucose >250 mg/dL                                      | 8 (2%)           | 8 (4%)   |
| Neutrophil <650/mm                                | 6 (1%)           | 3 (1%)   |

### 3.5 Duration of the Study

The study is expected to last a total of 20 months at each site. Enrollment of participants will take 6 months. Each individual participant will be followed for 12 months. Screening will start 1 month before enrollment. The study will remain open for 1 month after the last scheduled follow-up visit to allow follow-up on ongoing AEs and attempts to find participants that have not returned for their scheduled visits.

### 3.6 Withdrawal Criteria

#### 3.6.1 *Individual participants*

Participants withdrawn will not be replaced. A participant may be withdrawn early from the study for any of the following reasons:

- She considers it to be in her best interest
- A physician considers it to be in the participant's best interest because of safety reasons and/or for the well-being of the participant

Reasons for withdrawal from the study (and study product) will be recorded on the appropriate DCF. **When early withdrawal from the study occurs, every reasonable effort will be made to assess information relevant to the primary endpoints at the time of discontinuation.** This would include attempts to obtain specimens for HIV testing.

TDF is rated for use in pregnancy as category B: reproduction studies have been performed in rats and rabbits at doses up to 14 and 19 times the human dose based on body surface area comparisons and revealed no evidence of impaired fertility or harm to the fetus due to tenofovir. There are, however, no adequate and well-controlled studies in pregnant women. Because animal reproduction studies are not always predictive of human response, TDF should be used during pregnancy only if clearly needed. Pregnancy is an exclusion criterion for this study. We will use urine pregnancy tests monthly to monitor for pregnancy. Participants who become pregnant will have study drug withdrawn. We will attempt to monitor participants until the conclusion of the pregnancy and the outcome of the pregnancy will be reported to the Gilead Sciences Antiretroviral Pregnancy Registry, as described in the package insert for TDF.

#### **Study product interruption**

Treatment with the study product may be interrupted temporarily or permanently for any of the following reasons:

- The participant ran out of supplies for whatever reason (e.g., she missed a visit); in this case the date of interruption is the date of her last product use
- An adverse event
- The Investigator decides to withdraw the study product temporarily in the interests of the safety and well being of the participant

- The participant considers it to be in her best interest not to use the study product
- Pregnancy
- The participant becomes HIV positive

Whenever the study product is interrupted, the information will be noted on the follow-up DCF. For all except the first reason listed above, the date of the interruption is the date on which the Investigator decides to interrupt the treatment and if possible, follow-up should be continued until resolution of the AE. **If possible, participants will be tested for HIV so that the status is determined at the time of product interruption.**

Participants who have had study drug interruption may resume study product use and will be given the study product to which they were originally randomized. **At the time of product resumption the participant will be tested for HIV so that status is determined.**

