## 5.3 Monitoring of Product Compliance

Participants will return the unused tablets and bottle at each month's follow-up visit. Unused tablets will be counted and recorded on the appropriate DCF.

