#### ***7.6.4 Grade 1 serum creatinine elevation***

For the purposes of serum creatinine, the baseline value is defined as the last value prior to the administration of the first dose of study drugs. This value must be obtained from the laboratory. Serum creatinine values = 0.5 mg/dL above baseline should be confirmed by repeat testing within 3 calendar days of receipt of results and before study drugs discontinuation, unless such a delay is not consistent with good medical practice.

- For Grade 1 serum creatinine elevations, patients may continue study drug, but it is recommended that participants be monitored weekly until the serum creatinine returns to the original baseline value or  $\leq 0.3$  mg/dL from baseline.

(See Appendix 3 for details)

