#### ***7.6.5 Grades 2-4 serum creatinine elevations***

- Study drug should be permanently discontinued in the event that repeat testing of serum creatinine confirms a value equal to or higher than 2.1 mg/dL. The patient should be followed at periodic intervals not less than weekly, until the serum creatinine falls to within 0.3 mg/dL of the baseline value.

(See Appendix 3 for details)

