## 9.2 Analysis Plan Summary

A detailed analysis plan that covers both the final analysis and the planned interim analyses will be developed and approved prior to initiation of the study. The following is a summary of the planned analyses. Any deviations to be made from this summary plan will be documented in the detailed analysis plan.

All primary and most secondary analyses will be conducted on an intent-to-treat basis. However, in order to assess the effectiveness and safety of TDF among those participants who complied with key aspects of the study protocol and to evaluate the potential impact of treatment on loss to follow-up, various additional analysis populations may be defined in the detailed analysis plan. Any key decisions regarding the timing of outcomes, the appropriateness of test statistics or model assumptions, or any other statistical issues will be made in a masked review of the data (i.e., masked to the true treatment assignments). Unmasking with respect treatment assignment will only be done for the final interpretation of the results, unless otherwise required by the data monitoring committee (DMC) (see section 10.3).

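### Section 3.6.1 dates a participant's own decision to stop product by an Investigator decision that does not exist, so the recorded stop can be weeks late

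*Protocol*

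**What the plan says.** Under its heading on study product interruption, section 3.6.1 lists six reasons: running out of supplies, an adverse event, the Investigator's decision, the participant's own choice, pregnancy and HIV infection.

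- For a run-out, "in this case the date of interruption is the date of her last product use".
- For the other five, "For all except the first reason listed above, the date of the interruption is the date on which the Investigator decides to interrupt the treatment".
- One of those five is "The participant considers it to be in her best interest not to use the study product".

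Contact is monthly: under section 3.2, "HIV status will be monitored monthly", and section 8.3 places counselling, resupply and the product-use questionnaire at the same visits. Section 5.3 adds a monthly tablet count: "Unused tablets will be counted and recorded on the appropriate DCF". Neither 5.3 nor 8.3 names a last-dose date.

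Section 9.2 allows further analysis populations in the detailed plan, "in order to assess the effectiveness and safety of TDF among those participants who complied with key aspects of the study protocol". Section 9.2.1 makes the primary analysis intent-to-treat. If the Cox model is unsuitable, it falls back on cases divided by length of treatment exposure. Section 7.2 judges relatedness partly on timing relative to product administration. The clarifications to section 7.4 set a death-reporting window of 30 days from last product use or last evaluation, whichever is longer.

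**The concern.** The decision-date rule fits a stop that the Investigator orders. It does not fit a stop that the participant makes. She takes her last tablet at home, and no Investigator decision takes place that day. A site applying the rule literally has nothing to record except the day it learned of the stop and accepted it, which is likely to be the next visit. Sites may also resolve the gap in different ways. The run-out rule shows that last use was recognised as the relevant date where no decision exists, and a self-initiated stop has the same feature.

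This is a stated rule that yields a wrong date, not a detail left for later. An analysis plan cannot restore a last-tablet date that was never collected. A tablet count alone does not supply it: a woman given a bottle of 30 who returns 15 after 30 days may have stopped cleanly at day 15 or missed every second dose.

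At stake is the on- or off-product label for events near a stop, in any analysis that uses it. Section 3.6.1 also asks for HIV status at the time of interruption where possible. For a self-initiated stop, a test tied to the recorded date may come weeks after the last tablet.

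**Working it through.** **Inputs from the protocol.** 600 women per arm; visits about 30 days apart; placebo incidence 5 per 100 person-years; assumed true rate ratio 1 - 0.83 = 0.17, tested against 0.5; 30 infections required; 80% follow-up at 12 months (sections 3.2 and 9.1.1).

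**Assumptions, because the protocol gives no figures.** 10-20% of TDF women stop by their own choice. Stops are spread evenly between visits. The site dates the stop to the visit at which it learns of it. Incidence after the last tablet equals the placebo rate.

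**1. The plan's own figure.** Schoenfeld's formula with one-sided alpha 0.05, 90% power and ratio 0.17/0.5 = 0.34: 4 × (1.645 + 1.282)² / (ln 0.34)² = 34.3 / 1.164 = 29.4, so 30 events. The stated 30 is reproduced. The interruption date does not enter it.

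Expected TDF infections among 30, with equal person-time: 30 × 0.17 / 1.17 = 4.36.

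**2. Dating error per stop.** A stop spread evenly over a 30-day interval is recorded 0 to 30 days late, mean 15. With one missed visit it is 0 to 60 days late, mean 30.

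**3. Misdated time in the TDF arm.**

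| Self-initiated stops | Mean error | Person-years | Infections at 5/100 | Share of 4.36 |
|---|---|---|---|---|
| 60 (10%) | 15 days | 60 × 15 / 365.25 = 2.5 | 0.12 | 2.8% |
| 120 (20%) | 30 days | 120 × 30 / 365.25 = 9.9 | 0.49 | 11.3% |

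With loss running evenly to 20% at 12 months, an arm contributes about 600 × 0.9 = 540 person-years. The misdated time is therefore 2.5/540 to 9.9/540, or about 0.5% to 1.8% of the arm.

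**4. Infections whose label would change under the midpoint rule.** Section 9.2.1 dates an infection at the midpoint of the test interval. Only a stop in the first half of the interval can change the label. For a second-half stop the midpoint precedes the stop under either dating rule. A first-half stop leaves on average 22.5 days off and 7.5 days on product in a 30-day interval (45 and 15 in a 60-day interval). The on-product rate is 0.05 × 0.17 = 0.0085 per year.

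- 30 first-half stops, monthly visits: 30 × (22.5 × 0.05 + 7.5 × 0.0085) / 365.25 = 0.10 infections.
- 60 first-half stops, one visit missed: 60 × (45 × 0.05 + 15 × 0.0085) / 365.25 = 0.39 infections.

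**5. Fallback rate ratio, if the denominator is literally time on treatment.** Suppose only the TDF arm were affected and 540 recorded person-years included the misdated time. Correcting it multiplies the ratio by 540/(540 - 2.5) = 1.005 to 540/(540 - 9.9) = 1.019, so 0.170 becomes 0.171 to 0.173. If both arms are affected alike, the shift largely cancels.

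**The case against.** **No fixed analysis fails.** The primary analysis is intent-to-treat and ignores this date. Section 9.2 only permits complier populations, and the fallback applies only if the Cox model is unsuitable. Because section 9.2.1 also says intent-to-treat, its denominator may mean follow-up time. The section 7.4 window takes the longer of two dates, so for a woman who keeps attending the last evaluation will usually govern. All of this stands, and it limits the weight of the point.

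**Product use is recorded elsewhere.** Tablet counts and the questionnaire allow an approximate date, and the follow-up form, which is not shown, may hold a last-dose field. This stands in part: the protocol names no such field, and 3.6.1 instructs sites to record a different date as the interruption.

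**Other stops are dated well enough.** A reader might infer that all five decision-dated reasons are misdated, and that laboratory-triggered stops are dated too early because tablets continue until the woman is reached. The documents do not support this as a general claim. Pregnancy and HIV are tested at the visit, and the rapid test reads in 20 minutes (section 6.2). A creatinine value at the level set in section 7.6.4 "should be confirmed by repeat testing within 3 calendar days of receipt of results", and under section 7.6.5 "Study drug should be permanently discontinued in the event that repeat testing of serum creatinine confirms a value". The repeat brings the woman back into contact before the stop. A few days' gap is possible, but the protocol gives no figure for it.

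**Infections are not certainly mislabelled.** A reader might infer that every infection found at the visit after a self-initiated stop is falsely counted as on TDF. The infection date is itself imputed, and the infection may have been acquired before the stop. In step 4, the off-product part is 1.125 of 1.189 (22.5 × 0.05 against that plus 7.5 × 0.0085), or about 95%. That figure rests on the assumed rates and ignores any delay between acquisition and detectable antibody. Mislabelling is likely under those assumptions but not known for any one woman.

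**Conclusion.** The point holds for participant-initiated stops. Section 3.6.1 assigns them a decision date that does not exist for that reason, and with monthly contact the recorded stop can be up to about 30 days late, about 15 on average, longer after a missed visit. For the other reasons any gap is usually short.

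The size is modest. If 10-20% of TDF women stop themselves, about 2.5-10 person-years are misdated. That carries 0.12-0.49 expected infections, of which 0.10-0.39 concern intervals where the midpoint rule lets the label change. The upper ends require 20% to stop and all of them to miss a visit. The stop rate is an assumption throughout.

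A reader might infer that the trial's effectiveness conclusion is biased. It is not: the intent-to-treat Cox analysis and the 30-event target do not use the date. With only about four TDF infections expected, one changed label could still matter to a supporting on-product analysis. That, and the low cost of recording the right date, justify a change to data recording and nothing stronger.

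**What to change.** In section 3.6.1, define the interruption date for every reason as the date of the last tablet taken, by participant report checked against the section 5.3 tablet count. At minimum, apply this to participant-initiated stops. Keep the Investigator's decision date as a separate field, and record the date of the first tablet on resumption.

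The cost is one revised sentence and a few date fields on the follow-up form, with no added visits or tests. The reported last-tablet date will carry some recall error, which the tablet count can limit but not remove. No stopping rule or other clinical management changes.
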